#### Secondary implementation outcomes

As outlined in Table 3, secondary implementation outcomes will be guided by the heuristic defined by Proctor et al, 2010 (19), and will be assessed using facility-level administrative data and the indicators captured in the screening record register (Table 2), and supplemented with qualitative semi-structured interviews with the facility teams. Implementation metrics will include number of patients who refuse screening, number of patients who screen positive for depression, number of screen positive patients who are referred to the MO and number of patients who are initiated on treatment. Treatment initiation following referral to the MO is an important adoption outcome, and can involve provision of psychoeducation, prescription of antidepressant medication, referral to the brief psychosocial intervention (i.e., HAP) delivered by ASHAs, and/or referral to a specialist at the District Mental Health Program, Community Health Centre or private clinic.

The costs of delivering the Enhanced Implementation Support strategy in the intervention arm PHCs will be collected and categorized into the six building blocks of a health system based on the WHO's health system framework (45). This will include spending on health workforce for participating in the Enhanced Implementation Support strategy activities, such as time required to moderate (for the coaches) and participate (for the ANM/nurse) in the coaching sessions; and information technology, such as internet costs or phone bills for engaging in the coaching sessions. This data will be captured via time logs, payroll, and expense reports. Facility staff salaries will be collected from the National Health Mission reports on salary range for various health personnel in public health facilities. To clarify, the cost analysis will not evaluate the cost-effectiveness or involve a comparison of costs between the study arms because we are not able to collect cost data from the control arm given the irregular or need-based format of routine district team's support to the clinics for delivering depression care (refer, “Routine implementation support”), and because there is no additional implementation support being provided by our team for which the costs could be collected. We will be assessing only the cost of delivery of Enhanced Implementation Support strategy among the intervention arm clinics.

### Qualitative and observational data collection

At the end of the trial, qualitative interviews with facility teams, including ANMs/nurses and MOs, will be used to assess acceptability and feasibility of implementing the mhGAP depression care package across facilities in both arms. These interviews will focus on understanding experiences delivering depression care in both the intervention and control facilities, and to determine whether there may have been differing experiences in facilities receiving the Enhanced Implementation Support relative to control facilities receiving the Routine Implementation Support. The research team will also visit the facilities in-person to further collect observational and qualitative data about facility-level characteristics that may affect implementation of depression care, such as: facility staffing characteristics including workload, leaves, transfers and new appointments; the extent of dedicated physical space and the privacy of this space for conducting depression screening in the clinic; facility staff perceptions about asking questions included in depression screening, views about potential stigma, and about the materials posted in the clinics such as informational posters; MO attendance and their involvement in depression care activities; and screening rates of comparable NCD care programming. These visits will be coordinated in advance with the facility teams.

### Secondary patient outcomes

Table 4 lists patient outcomes that will be assessed at 3 months after enrolment. The proportion of enrolled patients with scores <5 on the nine-item Patient Health Questionnaire (PHQ-9), indicating remission (46), and functional outcomes using the WHO Disability Assessment Schedule (WHODAS 2.0) (47), and symptoms of anxiety using the Generalized Anxiety Disorder scale (GAD-7) (48), will be collected. A 2-week window for collection of follow up assessments from patients will be used to accommodate scheduling and logistics.

**Table 4 T4:** Secondary patient-level outcomes.

Measure	Source	Description	Rationale for selection	Hypothesis	Timeline
Depressive symptoms	Patient Health Questionnaire (PHQ) 9-item assessment tool Kroenke et al. (46)	PHQ-9 score can range from 0 to 27 since each of the 9 items can be scored from 0 (not at all) to 3 (nearly every day). A PHQ-9 total score of 10 or higher is indicative of depressive symptoms. A total score <5 indicates remission.	PHQ-9 can be entirely self-administered, yet, given the rural primary care context, it is feasible and simple to use for the ANM/nurse.	The proportion of patients showing remission linked to the primary health centers receiving enhanced implementation support is significantly lower at 3-month follow up than the proportion of patients showing remission linked to facilities receiving routine support.	3-month follow up
Functional outcomes	WHODAS 2.0 Üstün et al. (47)	WHODAS 2.0 captures the level of functioning in six domains of life including cognition—understanding and communicating; mobility—moving and getting around; self-care—attending to one's hygiene, dressing, eating and staying alone; getting along—interacting with other people; life activities—domestic responsibilities, leisure, work and school; participation—joining in community activities and participating in society.	WHODAS 2.0 is useful for brief assessments of overall functioning in surveys or health-outcome studies, *in situ*ations where time constraints do not allow for the application of the longer version—as may occur during baseline and end-line in this trial.	Patients at end-line in the intervention arm will have significantly lower scores on WHODAS 2.0, or improved functional outcomes, than patients in the control arm.	Baseline and 3-month follow up
Anxiety symptoms	GAD-7 Spitzer et al. (48)	This is a self-report scale, which is a screening tool and severity indicator for GAD. Items are rated on a 4-point Likert-type scale (0 = not at all, 1 = several days, 2 = over half the days, 3 = nearly every day). GAD-7 items describe some of the most salient diagnostic features of GAD (i.e., feeling nervous, anxious, or on the edge and worrying too much about different things).	GAD-7 was created to increase the identification of generalized anxiety disorder cases in the primary care setting. A cut-off score of 10 was identified as the optimal point for sensitivity (89%) and specificity (82%).	Patients at end-line in the intervention arm will have significantly lower scores on the GAD-7 than patients in the control arm.	Baseline and 3-month follow up

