**Methods:**

Employing a cluster-randomized hybrid type-III implementation trial design, 14 primary care facilities in Sehore district, Madhya Pradesh, will implement a collaborative depression care package based on the WHO's mhGAP program. Facilities will be randomized to either Enhanced Implementation Support or the Routine Implementation Support control condition. Enhanced Implementation Support consists of remote coaching and technical assistance, supplemented with in-person visits, and guided by the Plan-Do-Study-Act implementation cycles. The primary implementation outcome is the proportion of outpatients screened for depression by facility staff, with secondary outcomes including the proportions of outpatients who screen positive for depression, are referred to the medical officer, and initiate treatment. Secondary patient outcomes include proportion of patients who achieve reduction in depression symptom severity at 3-month follow up. Acceptability, feasibility, and fidelity of the depression care package will be assessed through routine observations collected during field visits, facility audits, and qualitative exit interviews with facility staff. Costs of delivering the Enhanced Implementation Support strategy will also be estimated.

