The teams at all 14 PHCs were trained on the World Health Organization's (WHO) mhGAP intervention guide (5), previously adapted for Sehore district (14). The MOs were trained through in-person and virtual modes, depending on their availability to attend in-person training, over eight days in the diagnosis, treatment and referral of positive cases of depression, including the option for referring patients to receive HAP delivered by ASHAs (29). The training for ANMs and nurses was conducted separately, as part of a 2-day in person training with instruction on screening of outpatients for depression, and referral and tracking of depression cases. Training for ANMs and nurses emphasized case detection and screening outpatients using the PHQ-2, and entering data into a “Screening Record Register” to track screening rates, refusal, patient willingness to be contacted by the research team (to participate if they screen positive), and referral to the MO and initiation of treatment. The PHQ-2 is a screening questionnaire for depression which comprises two items of the widely used and contextually validated PHQ-9. The PHQ-2 was selected to increase the quality and efficiency of screening conducted by ANMs/Nurses, and its use, instead of the full 9 item version, is supported by prior studies showing that the positive predictive value for the presence of “any depressive disorder” is 75% for a score of ≥3 (38). Further, the health system in India has planned to adopt the PHQ-2 for community-level depression screening (39). Each trial arm will have 7 PHCs, with estimated total staffing of 14 MOs (2 per facility), 14 nurses (2 per facility), and 7 ANMs (1 per facility), with some variation in staffing expected between facilities.

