### Participant recruitment

Adult outpatients (age ≥18 years) of any gender who screen positive for depression (PHQ-2 ≥ 3) at participating PHCs will be invited to enroll in this trial. Outpatients will be excluded if they have significant speech, hearing, language or cognitive impairment impacting their ability to provide informed consent and complete study assessments, those needing urgent medical or psychiatric attention, those not planning to stay in the study catchment area for at least three months (for participation in the clinical outcome assessment), or those who do not understand Hindi.

The ANM/nurse will be the first point of contact for determining a patient's willingness to participate in the study. After screening on the PHQ-2, if a patient is screened positive (score ≥3), they are potentially eligible to participate in the clinical care component of the trial. Prior to referral to the MO, the ANM/nurse will mention the study to the patient and ask whether they are willing to be contacted to learn more (Figure 1). If the patient agrees, the ANM/nurse will record their name, address, and contact number to share with the study team. The study data manager will retrieve the data on patient willingness to be contacted during weekly review of facility screening activities, and share this data with a study research assistant. The research assistant will call the patient to introduce the study, and determine whether the patient is interested. If the patient assents, the research assistant will meet the patient within 7 days (up to a maximum of 2 weeks) at the patient's home or a mutually agreed location (e.g., PHC) to confirm eligibility, collect informed consent, and complete baseline assessment.

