### Statistical analysis

All analyses of implementation outcomes will be intention-to-treat comparisons between arms. Generalized linear regression models with a log link will be used to compare facility-level implementation outcomes, including the primary outcome of proportion of patients screened on the PHQ-2. ANCOVA analyses will be conducted for comparing secondary implementation outcomes between arms. Time by study arm interactions will be explored using a growth curve model to inspect non-linear trends in the progress of the screening, number of patients who screen positive, referral to MO and treatment initiation. Descriptive statistics will be used for comparing exploratory measures of facility readiness and context assessment between arms. The process indicators from the PDSA coaching sessions will be used for descriptive analysis, to quantitatively assess fidelity to the protocol for Enhanced Implementation Support. Logistic regression models will be used to compare the proportion of patients who remit on the PHQ-9, defined as score <5, between arms at 3-month follow-up. Possible covariates will be entered into the models, including age or gender of the patients, as well as adjusting for cluster effects. Linear regression models will be used to assess differences in the change in disability (WHODAS 2.0) and anxiety (GAD-7) outcomes at 3-month follow up, with baseline values as covariates to adjust for any baseline inter-cluster differences. Stata version 17.0 will be used for all statistical analyses and *p*-values <0.5 will be considered statistically significant.

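### Remission is PHQ-9 below 5 at 3 months in patients who enter on PHQ-2 alone, with no stated baseline depression adjustment, so arm differences in severity at entry can pass as a remission effect

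*Protocol article*

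**What the plan says.** All references are to the protocol article.

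- **Entry (Participant recruitment):** adults whose PHQ-2 score is 3 or more at a trial facility are asked to join. Exclusions follow (impairment, urgent need, leaving the area, no Hindi), but no minimum PHQ-9 is listed. A baseline assessment follows consent, within 7 days and at most 2 weeks. Its instruments are not listed.
- **Outcome (Secondary patient outcomes):** "The proportion of enrolled patients with scores <5 on the nine-item Patient Health Questionnaire (PHQ-9), indicating remission". Table 4 adds: "A PHQ-9 total score of 10 or higher is indicative of depressive symptoms. A total score <5 indicates remission". The cut-off of 10 is used neither for entry nor to define who is analysed.
- **Timing (Table 4):** the PHQ-9 row ends "linked to facilities receiving routine support. 3-month follow up". The WHODAS and GAD-7 rows both end "than patients in the control arm. Baseline and 3-month follow up".
- **Model (Statistical analysis):** "Logistic regression models will be used to compare the proportion of patients who remit on the PHQ-9". Candidate covariates are given as a non-exhaustive list naming age or gender, plus adjustment for clusters. Baseline values are named as covariates only for the linear models of WHODAS and GAD-7.
- **Abstract (Methods):** the outcome is given instead as the "proportion of patients who achieve reduction in depression symptom severity at 3-month follow up".
- **Screening accuracy (Facility eligibility and recruitment):** to justify the PHQ-2, the article cites earlier research in which 75% of people scoring 3 or more had some depressive disorder.
- **Limitations:** possible selection bias in the patient outcomes is acknowledged. No adjustment for it is named.

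**The concern.** A score below 5 at 3 months shows remission only in someone who was above that level to begin with. Entry on PHQ-2 does not ensure this, and the outcome carries no baseline condition.

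That would add little bias if the two arms enrolled similar patients, but cluster randomisation does not secure this here. Patients are found after allocation by nurses and auxiliary nurse midwives who know their arm, and the intervention acts directly on how many people those staff screen. Blinding the outcome assessors protects the 3-month measurement, not the make-up of the enrolled group. Adjusting for clusters deals with correlation within facilities, not with a systematic difference in case mix between arms.

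At stake is the trial's only depression outcome in patients. A difference in remission, or its absence, could reflect who was enrolled rather than how they fared. The article adjusts the other two patient scales for baseline and does not say so for this one.

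**Working it through.** **Plan's own figure.** The article gives no expected remission rate, sample size or power for this outcome, so there is nothing to reproduce.

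**Step 1: can a patient enter already below 5?** The PHQ-2 is two items of the PHQ-9, each scored 0 to 3. If the PHQ-2 is 3 and the other seven items are 0, the PHQ-9 is 3. The minimum PHQ-9 at entry is therefore 3, which is below 5. The documents do not say how many patients score 3 or 4.

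**Step 2: share of non-cases.** With a positive predictive value of 75%, the share of screen-positives without any depressive disorder is f = 1 - 0.75 = 0.25. This comes from prior studies, not from this trial's enrolled patients.

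**Step 3: effect on the outcome.** Let r1 be the proportion below 5 at 3 months among cases and r0 the proportion among non-cases, the same in both arms (no treatment effect). Then:

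- Overall proportion below 5 = f × r0 + (1 - f) × r1
- Non-cases among those counted as remitted = f × r0 / [f × r0 + (1 - f) × r1]
- False arm difference = (f in one arm - f in the other) × (r0 - r1)

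The documents give neither r0 nor r1. I assumed 20-40% for cases and 50-80% for non-cases, and used five pairs within that range:

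| r1 | r0 | Overall at f = 25% | Non-cases among remitted | False difference, 35% v 25% | Odds ratio, 35% v 25% | False difference, 40% v 25% |
|---|---|---|---|---|---|---|
| 20% | 60% | 30% | 50% | 4 points | 1.20 | 6 points |
| 30% | 50% | 35% | 36% | 2 points | 1.09 | 3 points |
| 30% | 70% | 40% | 44% | 4 points | 1.18 | 6 points |
| 40% | 60% | 45% | 33% | 2 points | 1.08 | 3 points |
| 40% | 80% | 50% | 40% | 4 points | 1.17 | 6 points |

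First row in full: 0.35 × 0.60 + 0.65 × 0.20 = 0.34, against 0.25 × 0.60 + 0.75 × 0.20 = 0.30, a difference of 4 points.

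The extreme corners of the assumed range are wider. For a 10-point difference in f, 0.10 × (0.50 - 0.40) = 1 point and 0.10 × (0.80 - 0.20) = 6 points. The sign reverses if the other arm has more non-cases: 15% against 25% gives -2 to -4 points for the same five pairs.

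**Step 4: is there a route to unequal f?** Sample size estimation assumes 10% screened under routine support and 25% under enhanced support, a ratio of 25 / 10 = 2.5. Who is reached may change along with how many. The documents do not say in which direction severity would move.

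**The case against.** **Baseline PHQ-9 may exist.** The content of the baseline visit is not listed. Limitations says the team considered placing baseline and endpoint PHQ-9 assessments in routine facility work and dropped the idea because of workload. What was rejected is facility staff doing it, which leaves room for a PHQ-9 at the research visit. The abstract's wording about reduction fits that too, and remission is by nature read at 3 months, which may explain the Table 4 entry. This stands: it cannot be said that no baseline PHQ-9 was taken.

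**The covariate list is open.** The article does not limit the model to age, gender and cluster, and a final list is commonly left to the statistical analysis plan. This also stands. But the article does fix baseline adjustment for two of its three patient scales, so the missing statement for the third is more than brevity.

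**Non-case does not mean below 5.** Lacking a disorder is not the same as a PHQ-9 under 5, and a total of 3 or 4 at entry needs near-zero scores on seven items. A reader might infer that a quarter of enrolled patients would count as remitted whatever their care. The documents do not support that.

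**Direction and size.** A reader might also infer that wider screening makes the enhanced arm's patients milder and produces a false benefit of 7 to 9 points. Those figures need 35% of cases and 80% of non-cases below 5, with non-case shares of 25% v 40% (46.25% v 53%) or 15% v 35% (41.75% v 50.75%). None of these inputs is in the documents. Both arms use the same PHQ-2 threshold, and screening more people does not by itself change severity among those who screen positive.

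**Already disclosed, and secondary.** Selection bias is acknowledged, and a hybrid type III trial puts less weight on patient outcomes. Both are true. The acknowledgement names no adjustment and does not touch the endpoint definition.

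**Conclusion.** The point holds as a gap in how the remission comparison is specified. Three things rest on the text alone: entry on PHQ-2 without a PHQ-9 minimum, remission below 5 with no baseline condition, and baseline measurement and adjustment stated for WHODAS and GAD-7 but not for the depression outcome. The abstract describes a different outcome, because a reduction needs a baseline score and a score below 5 does not.

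The bias is a risk in either direction, not an established fact. Its size rests on assumed rates: about 2-4 points for a 10-point arm difference in non-case share (odds ratio 1.08-1.20), and 3-6 points for 40% v 25%, over the five pairs used. It affects a secondary outcome; the primary screening result is untouched.

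**What to change.** 1. Prespecify baseline PHQ-9 as a covariate in the logistic remission model, matching the treatment of WHODAS and GAD-7, and state whether PHQ-9 was taken at the baseline visit.
2. If it was not taken, adjust for baseline GAD-7 and WHODAS, and for the PHQ-2 score if the register holds it.
3. Report remission among patients with baseline PHQ-9 of 10 or more as a sensitivity analysis only. The baseline visit comes after randomisation and up to 2 weeks after screening, when treatment may have begun, so restricting the main analysis on it could add bias of its own. It would also drop milder patients.
4. Align the abstract with the remission definition.

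**Cost:** plan wording and slight extra analysis, using data already collected. Trial status records closeout in April 2024 with primary analyses to follow, so no new baseline data can be obtained. Adjustment reduces the selection bias but does not remove it, and the baseline scores carry the timing caveat in item 3 when used as covariates too.

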### Exploratory outcomes

The Organizational Readiness for Implementing Change (ORIC) (49) will be used to assess readiness of the PHCs for implementing the depression care package. This 12-item survey is based on Weiner's theory of organizational readiness for change and covers two core constructs—change commitment (5 items) and change efficacy (7 items). The Atlas Initiative Toolkit will be used to assess facility-specific implementation factors (50). The toolkit includes two surveys, beginning with the Progress Survey followed by the Post-Implementation Survey. The surveys are based on an organizational readiness heuristic, abbreviated as R = MC2 (51), which defines organizational readiness for an innovation (R) as a function of three components: motivation to implement an innovation (M), the general capacities of an organization (C), and the innovation-specific capacities needed for a particular innovation (C). The surveys were translated and adapted for use in Madhya Pradesh, India, and will be collected from the MOs and ANMs/nurses involved in delivering depression care. The Progress Survey will be collected before trial launch to assess contextual factors that may impact the readiness to implement depression care. This survey captures the internal culture of the facility, which is not expected to change soon after initiating the Enhanced Implementation Support strategy. The Post-Implementation Survey will be collected from the same facility staff about one month before the end of the 12-month active intervention phase to assess the need for modifications to the implementation strategy.

